#### Study Design

Pre- and poststudy assessments were conducted, with comparison of pre- and postimplementation of a program for psychosocial assessment.

#### Participants and Data Collection

Pregnant women who could communicate in Swedish and who were enrolled in early pregnancy at maternity clinics in the Västmanland Region were invited to participate in the study. In the poststudy, patients from all 25 maternity clinics in the region were invited to participate. The women were sent an envelope by post with an invitation to participate, a consent form, and a questionnaire. Consent covered the review of medical records (objectives 2 and 3) and questionnaire data (objective 4).

Participant inclusion was completed in 2022. Pre-implementation (2019), a request for participation was sent to 887 patients, and 487 were included. Questionnaire 2 was sent to 512 patients, and 314 responded to both questionnaires 1 and 2. Postimplementation (2020-2021), a request for participation was sent to 2368 patients, and 942 were included. Questionnaire 2 was sent to 837 patients, and 708 responded to both questionnaires 1 and 2.

A review of medical records will be conducted in the specific data system for antenatal and perinatal health care used in the region, to extract data for objective 2.

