According to the different guidelines, various implementations concerning antenatal and perinatal mental health have been established in different regions of Sweden. In Västmanland Region, a program for psychosocial assessment during pregnancy was implemented in spring 2020, according to national and international recommendations [16,21,24,25]. The purpose of the implementation was to provide women with appropriate interventions as early as possible during pregnancy, achieve equity in health care, decrease the postpartum depression rate, facilitate the midwives’ work, and develop collaborations between midwives and psychologists. The model used during the implementation process is closely aligned with the Quality Implementation Framework [26,27], and its phases correspond well to those applied in our implementation. The Quality Implementation Framework offers a comprehensive, structured approach for guiding the implementation process, with a focus on facilitating the translation of evidence-based practices into real-world settings [26]. In addition, our implementation process and associated strategies draw upon elements from other established process models and frameworks; however, the effectiveness or outcomes of the implementation itself will not be evaluated in this study.

Although guidelines have been published and various working methods have been implemented across Swedish regions, there is still a lack of evidence supporting a specific method, and no national consensus has been established regarding the most appropriate approach. Moreover, no scientific evaluation has yet been conducted to assess the effects of implementing a program to identify mental ill-health during the perinatal period in Sweden, despite its presumed importance for informing clinical practice. Although several countries have developed clinical guidelines for addressing perinatal mental health, their implementation and evaluation in practice remain insufficiently unexplored, both in Sweden and internationally. This limits our understanding of how to translate these guidelines into routine care and optimize outcomes for mothers, families, and health care systems. To address this knowledge gap, this project was initiated alongside the program’s implementation, to evaluate its effectiveness from both patient and professional perspectives.

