#### Implementation Strategies

We involved 15 midwives and several psychologists in the design and adaptation of the program, as well as a pilot project to facilitate implementation in clinical practice. The program for psychosocial assessment was created concurring in content with, but actually preceding, the aforementioned national recommendations. The midwives’ experiences and opinions were recorded during meetings, and additional adjustments were made based on their suggestions for improvement. The adjustments were as follows: In addition to being asked in early pregnancy, all pregnant women are asked the questions about mental health (including the Whooley questions [30] and Generalized Anxiety Disorder 2-item [GAD-2] [31], see the following sections) again at gestational week 33. Those identified with mental ill-health and illness during pregnancy are asked again postpartum; in-depth questions concerning thoughts and feelings about childbirth, aimed at identifying fear of childbirth, are included; and the timing of questions concerning exposure to violence (already part of the health care program prior to the introduction of the program) was altered.

To carry out the implementation, the clinics’ funding was increased according to experiences in the pilot project. During the implementation, the need for contact with the psychologists also increased, and additional funding for psychological treatment was thus provided.

The program was developed, and supporting material was created to facilitate the midwives’ work. Collaborations between psychiatrists, obstetricians, general practitioners, and psychologists were established to clarify the referral pathways for women with identified mental illness or ill-health. Establishment of a multidisciplinary consulting team was reinforced with the aforementioned professionals, to provide guidance for the midwives regarding the management of the women identified with severe mental illness, as well as to strengthen the collaboration with other health care providers.

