**Figure 1 figure1:**
[figure not shown]
Overview of the program for psychosocial assessment (Västmanland Region), including maternity clinic visits and questions about mental health and social factors at various gestational weeks (+days); the visits after the dashed line (postpartum) will not be included in this evaluation. EPDS: Edinburgh Postnatal Depression Scale; GAD-2: Generalized Anxiety Disorder 2-item.

At the first visit (gestational weeks 5-7), the midwife asks all women questions about prior and ongoing serious mental illness or perinatal mental illness and treatment, as well as family history of serious mental illness or perinatal mental illness. At the second visit, which takes place a few weeks later (gestational weeks 8-12), questions are asked concerning prior and ongoing less serious mental ill-health, symptoms of stress and anxiety, social situation, support from relatives and network, and experiences with domestic violence.

Moreover, to specifically identify symptoms of depression and anxiety during the conversation about mental ill-health, the midwife asks all women the Whooley questions [30] and GAD-2 questions [31].

The Whooley questions are designed to identify symptoms that may be present in depression. The questions are as follows:

During the past month, have you often been bothered by feeling down, depressed, or hopeless?During the past month, have you often been bothered by little interest or pleasure in doing things?

The GAD-2 is a brief initial screening tool aimed at identifying symptoms of anxiety. The questions are as follows:

Over the last two weeks, how often have you been bothered by feeling nervous, anxious, or on edge?Over the last two weeks, how often have you been bothered by not being able to stop or control worrying?

If the woman responds in the affirmative to any of these 4 questions, the Edinburgh Postnatal Depression Scale (EPDS) [32] is administered to aid further assessment [2,21,24]. The EPDS is a comprehensive 10-item self-rated scale for identifying symptoms of depression [32]. It has been validated in Sweden for use during pregnancy [33].

The Fear of Birth Scale [34,35] is a self-rated scale administered at gestational week 24 to identify fear of birth. If needed, additional visits are offered for childbirth preparation. There is also the possibility of referral to the Obstetrics Department’s specialist unit for assessment and care planning with a midwife, obstetrician, and perinatal psychologist.

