#### Statistical Analysis

For objective 2, survival analysis will be used to assess differences in the timing of mental ill-health identification during pregnancy. Group comparisons will be performed using Cox proportional hazards regression analysis, including an indicator variable for pre- versus postimplementation. The model will be adjusted for potential confounders (eg, age, primiparous women, civil status, employment status, maternity clinic), selected according to the disjunctive cause criterion [38].

The effect measure will be the hazard ratio with 95% CIs.

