#### Participants and Data Collection

Regarding objective 4, participant inclusion and data collection have been completed, and data management and analysis are ongoing. Participant inclusion was performed according to the description in objective 2. In the 2 different patient groups, pre- and postimplementation questionnaires were sent twice during pregnancy. The first questionnaire was administered in early pregnancy after the first 2 visits to the midwife, and the second questionnaire was administered after gestational week 33.

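### Any preimplementation woman recruited late in 2019 could reach later programme elements and the pandemic while the fixed pre/post indicator still counts her as unexposed

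*Protocol article*

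**What the plan says.** All places are in the Protocol article.

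- **Who is in the comparator.** Objective 2, Participants and Data Collection: "Pre-implementation (2019), a request for participation was sent to 887 patients, and 487 were included". No months are given. The other group follows directly: "Postimplementation (2020-2021), a request for participation was sent to 2368 patients, and 942 were included". Objectives 3 and 4 use the same women.
- **When they entered.** Objective 4, Participants and Data Collection: "The first questionnaire was administered in early pregnancy after the first 2 visits to the midwife". The programme description places the second visit at weeks 8 to 12: "At the second visit, which takes place a few weeks later (gestational weeks 8-12".
- **When outcomes are observed.** Objective 2 analyses the timing of identification in pregnancy, and Objective 3 includes treatment begun in pregnancy and referral pathways. For Objective 4, "the second questionnaire was administered after gestational week 33". Postpartum assessments are excluded.
- **When the programme began.** Guidelines and Recommendations section: "a program for psychosocial assessment during pregnancy was implemented in spring 2020". Under Implementation Strategies, "all pregnant women are asked the questions about mental health" not only early on but again at week 33. The same section describes clarified referral pathways, a reinforced consulting team and extra funding for psychological treatment.
- **When the pandemic began.** Study Status dates the outbreak to the first quarter of 2020.
- **How exposure is coded.** The Objective 2 Cox model is specified as "including an indicator variable for pre- versus postimplementation". No censoring at programme start and no time-dependent exposure is described.

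**The concern.** Group membership is fixed at entry, but outcomes build up over the following five to seven months. A woman who entered late in 2019 was in mid or late pregnancy when the programme and the pandemic arrived. She could have been asked the week-33 questions or referred along the new pathways, and could have answered questionnaire 2 under pandemic conditions. The analysis would attribute all of this to the period without the programme.

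For Objective 2, which is primary, late identifications prompted by the programme would be credited to the comparator and pull the hazard ratio towards 1. For Objective 3, the new pathways and funding are close to what is being measured, so the contrast would shrink in the same way. For Objective 4, some comparator answers on current mental health and help received could come from the programme and pandemic period. Objective 1 leaves out 2020 between its two register periods; Objectives 2 to 4 have no such gap.

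This is separate from slow roll-out in the postimplementation group. The listed covariates (such as age, parity, civil status, employment and clinic) cannot repair exposure time that is assigned to the wrong period.

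**Working it through.** **1. The plan's own figure.** Objective 2 states 142 events, two-sided 5% significance, 80% power and a detectable hazard ratio of about 1.65 (Schoenfeld). The preimplementation share is 487/(487 + 942) = 0.341.

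- √(142 × 0.341 × 0.659) = 5.65
- Detectable HR = exp[(1.960 + 0.842)/5.65] = 1.64
- Power at HR 1.65 = Φ(5.65 × ln 1.65 − 1.960) = 81%

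The stated figure reproduces, so it can serve as the baseline.

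**2. Calendar check.** Cut-off entry date = programme start − (w − g) weeks. Here g is gestational week at entry and w is 33 (questions and questionnaire 2) or 40 (taken as the end of pregnancy). Women entering after the cut-off reach week w after the start. The share is the days from the cut-off to 1 January 2020, divided by 365.

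Assumptions not in the documents: g = 8 to 12, even recruitment over 2019, and spring 2020 read as 1 March to 31 May. Each cell runs from g = 8 to g = 12.

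| Programme start | Week-33 cut-off | Share (of 487) | Week-40 cut-off | Share (of 487) |
|---|---|---|---|---|
| 1 March 2020 | 8 Sept to 6 Oct 2019 | 32% to 24% (153 to 116) | 21 July to 18 Aug 2019 | 45% to 37% (219 to 181) |
| 1 April 2020 | 9 Oct to 6 Nov 2019 | 23% to 15% (112 to 75) | 21 Aug to 18 Sept 2019 | 36% to 29% (177 to 140) |
| 31 May 2020 | 8 Dec 2019 to 5 Jan 2020 | 7% to 0% (32 to 0) | 20 Oct to 17 Nov 2019 | 20% to 12% (97 to 60) |

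Example: from 8 September 2019 to 1 January 2020 is 115 days, and 115/365 = 32%.

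**3. The extremes.** A woman entering on 31 December 2019 reaches week 33 between 26 May and 23 June 2020, and week 40 between 14 July and 11 August 2020. If recruitment ended before about 21 July 2019, nobody reaches week 33 or week 40 after any start from 1 March. If it ran only from July to December 2019 (184 days), the largest week-33 share is 115/184 = 63%.

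**4. How long recruitment may have taken.** The region had 8246 births in 2017 to 2019, or 8246/36 = 229 a month. The 887 invitations equal 887/229 = 3.9 months of births, so recruitment need not have filled the year. Where such a window would lie is not stated.

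**5. Upper bound on dilution in Objective 2.** Under the assumptions of step 2, a fraction f of 1.4% to 16.3% of preimplementation follow-up (entry to week 40) falls after the start. If that time carried the full programme effect, the apparent HR is 1.65/(1 − f + 1.65f).

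- f = 0.014: HR 1.64, power 79%
- f = 0.163: HR 1.49, power 62%

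These women had already passed visits 1 and 2, so the true dilution would be smaller.

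**The case against.** The strongest reply is that the premise is conditional. No section says that anyone was recruited late in 2019, and the figure giving the study periods is not shown in the copy reviewed, so the months may be stated there. The programme's core assessment sits in visits 1 and 2, which these women had completed. Only the week 24 Fear of Birth Scale and the week 33 questions were still ahead, and nothing says that women in mid-pregnancy were moved onto the new schedule. The article also reports early adherence problems and slow implementation, so the effective start may have been later than spring 2020. The programme bias runs towards no effect and cannot manufacture a benefit. The pandemic is acknowledged as a confounder, and censoring rules are often left to a fuller document.

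Most of this stands and limits the size of the point. It does not remove it. The referral pathways, consulting team and treatment funding were not tied to visits 1 and 2, so they could reach women already pregnant. The pandemic passages discuss confounding in general and do not mention 2019 recruits crossing into 2020. The Strengths and Limitations section says that the analysis will need ways to account for the pandemic, but names none.

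A reader might infer that a sizeable part of the comparator did pass into the programme and was followed to birth as unexposed. The documents do not support that as fact: recruitment months are not given, actual exposure of these women is not described, and follow-up to birth is only inferred from the reference to pregnancy as the observation period.

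**Conclusion.** The point holds as a conditional gap. The stated dates make overlap unavoidable for any woman recruited in the last weeks of 2019, the fixed indicator would misclassify that time, and no handling is described. The number affected cannot be determined from the article. It is 0% if recruitment ended by about mid-July 2019. It is about 0% to 32% reaching week 33 after the start under even recruitment, entry at weeks 8 to 12 and a start between 1 March and 31 May 2020. It would be higher if recruitment was concentrated late in the year.

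For the programme effect, any bias is partial and conservative; even the upper bound leaves an apparent hazard ratio of 1.49 where the truth is 1.65. With power of only about 81% at that effect, such a loss would matter for a primary objective. The direction of any pandemic effect on the comparator cannot be settled from the documents.

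**What to change.** State the months of recruitment in 2019 and the programme start date, for the region or by clinic if known. If they show no overlap, one sentence closes the matter. Otherwise:

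- **Objective 2:** censor preimplementation women at programme start in the Cox model, or make exposure time-dependent. Censoring is the cleaner choice, because late recruits who missed the programme's visits 1 and 2 are not fully exposed afterwards. Pandemic time before programme start remains and should be acknowledged.
- **Objective 3:** do not cut off treatment and referral counts at programme start in the preimplementation arm alone. That would shorten the window in one arm of a comparison of proportions, lower its proportion artificially and favour the programme. Instead restrict the comparator to women whose pregnancy ended before programme start, at least as a sensitivity analysis.
- **Objective 4:** repeat the questionnaire 2 comparison without preimplementation responses given after programme start.

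Objectives 2 and 3 data collection is planned for 2025 to 2026, so their rules can be fixed before analysis. The change is to analysis wording and needs only dates; start dates by clinic are not given in the article and may not be available. The cost is precision in the smaller arm. Under even recruitment, Objective 2 loses 1% to 16% of preimplementation follow-up. The Objective 3 restriction would drop 12% to 45% of that arm, which is why it may serve better as a sensitivity analysis. In Objective 4, if the 314 women who answered both questionnaires are spread in the same way, up to about 99 responses (314 × 115/365) would be set aside.

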#### Challenges in the Implementation

The maternity clinics in Västmanland Region are scattered throughout the county, and many clinics are quite small. As elsewhere in Sweden, there has also been a shortage of midwives in the region for several years. Combined with a vulnerable organization, this initially led to some difficulties in ensuring adherence and fidelity to the program, and implementation took longer than expected. A plan was conducted to facilitate the implementation process, with continuous information and education, support, and follow-up. The implementation process also took place during the COVID-19 pandemic, another aggravating circumstance.

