Furthermore, addressing the recruitment challenges faced for objectives 2-4, it is crucial to note the difficulties encountered in achieving the initial target sample size. Specifically, we aimed to recruit 640 participants in the pre-implementation phase but were only able to enroll 487. This shortfall contrasted with the implementation phase, during which we successfully recruited 942 participants.

Given the research design outlined in the preceding paragraphs, together with the collected data, this will provide the opportunity to test a wide array of hypotheses in the current research area. Specifically, it is suitable for testing hypotheses involving both dichotomous outcomes, with lower or higher pre-implementation prevalence, and a wide range of continuous outcomes, including when testing for small, standardized differences.

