#### Participants and Data Collection

Data will be extracted from the SPR for all registered pregnant individuals in the Västmanland Region, preimplementation (2017-2019) and postimplementation (2021-2023) of the program. We chose 3-year periods for data extraction in order to obtain more representative data concerning any changes, as well as to counteract the effects of the COVID-19 pandemic.

The SPR is a national quality register with certification level 1 (the highest level). This accessibility is a prerequisite for the development of health care and consequently, for improving the health of pregnant women and their children, as well as promoting equitable care and high quality in the chain of care. Improvement work is facilitated by rapid feedback of SPR data and results. The SPR is a rich source for research in the field of pregnancy and childbirth. Of the 99,011 births registered in Sweden in 2023, 97,964 were registered in the SPR, a coverage rate of 98.9% [7].

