## Results

### Study Status

The recruitment of participants for objectives 2-5 is complete. Data collection for objectives 1-3 is planned for 2025-2026, with compilation of the results during 2026. Data collection for objective 4 was completed in 2022, and data analysis and compilation of the results are planned to be conducted in autumn 2025. Data collection for objective 5 was completed in 2024, and analysis and compilation of the results are also planned for autumn 2025.

The data collection for objectives 2-4 was extended in scope and time, as implementation took longer than estimated due, among other factors, to the COVID-19 pandemic outbreak in the first quarter of 2020 [43]. The pandemic was expected to create temporarily elevated levels of mental ill-health and illness, especially during pregnancy. Health care services in Sweden introduced restrictions for pregnant women’s partners accompanying them during and after pregnancy, which might have affected both expectant parents.

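### Objectives 2-4 treat everyone recruited in 2020-2021 as postimplementation, although the programme began only in spring 2020 and was slow to bed in, so part of the group may have been only partly exposed

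*Protocol article*

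**What the plan says.** The article's section on Swedish guidelines dates the start: "a program for psychosocial assessment during pregnancy was implemented in spring 2020". Under Challenges in the Implementation it describes small, scattered, short-staffed clinics and says "this initially led to some difficulties in ensuring adherence and fidelity to the program, and implementation took longer than expected". Study Status links this to recruitment: "The data collection for objectives 2-4 was extended in scope and time, as implementation took longer than estimated".

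Objective 2 nevertheless sets the groups by calendar period. The earlier group is "Pre-implementation (2019), a request for participation was sent to 887 patients, and 487 were included"; the later one is "Postimplementation (2020-2021), a request for participation was sent to 2368 patients", of whom 942 were included. Objectives 3 and 4 take over the same participants. The Objective 2 Cox model has one indicator for pre against post. Objective 3 compares referrals before and after, and Objective 4 is likewise described as a pre/post comparison. No roll-out level, clinic start date or separate handling of 2020 recruits is stated for any of them.

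Objective 1, the other primary objective, uses "preimplementation (2017-2019) and postimplementation (2021-2023) of the program", so 2020 belongs to neither of its periods.

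**The concern.** The two primary objectives attach the word postimplementation to different stretches of the programme's life. In Objectives 2-4 the label starts in the year the programme was introduced, when by the article's own account delivery was still difficult. A two-level indicator gives a woman seen at a clinic not yet delivering the programme the same exposure as one seen after it was established. Adjusting for maternity clinic does not separate early from later recruits within a clinic.

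Two things are at stake. A null or weak Objective 2 result could not be told apart from incomplete roll-out. And Objectives 1 and 2 would be read together although their later periods differ, with no explanation of why.

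**Working it through.** **Inputs.** From Objective 2, Participants and Data Collection: 487 women pre and 942 post, 1429 in all. From Objective 2, Statistical Power: 142 events, 2-sided 5% level, 80% power, detectable hazard ratio about 1.65 by the Schoenfeld method. The 142 is taken as stated. The share f of the 942 not effectively exposed is **not in the documents**; 10%, 25% and 50% are assumptions chosen to show a range.

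**Step 1: reproduce the plan's figure.** With a = 487/1429 = 0.341, the detectable hazard ratio is

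HR = exp[(1.960 + 0.842) / sqrt(142 × 0.341 × 0.659)] = exp(2.802 / 5.65) = 1.642.

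Power at exactly 1.65 is Φ(ln 1.65 × 5.65 − 1.960) = 80.7%. The stated figure reproduces, with almost no slack.

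**Step 2: keep the unexposed women in the post group.** Give a share f a hazard ratio of 1 and the rest 1.65, so that the observed ratio is about 1 + (1 − f) × 0.65. Hold events at 142 and apply the power formula from Step 1.

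**Step 3: leave those women out.** The post group becomes 942 × (1 − f), events are scaled to the remaining sample, 142 × (487 + 942(1 − f)) / 1429, a is recalculated, and the true ratio of 1.65 is kept.

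| f (assumed) | Observed HR, all 942 | Power, all 942 | Post women left | Events left | Power, those women left out |
|---|---|---|---|---|---|
| 0 | 1.65 | 81% | 942 | 142 | 81% |
| 10% | 1.59 | 74% | 848 | 133 | 79% |
| 25% | 1.49 | 61% | 706 | 119 | 76% |
| 50% | 1.33 | 36% | 471 | 95 | 69% |

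**Step 4: sensitivity to the mixing rule.** Averaging on the log scale, 1.65^(1 − f), gives 1.57, 1.46 and 1.28, with power 72%, 56% and 29%. The picture is the same and slightly worse.

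The table assumes that the affected women got no effect at all and could be identified exactly. Partial exposure would dilute less, and a date-based split would sort women less cleanly. It also isolates one bias: the pandemic is not in it.

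**The case against.** The best defence is that overlap between roll-out and recruitment is inferred. The article gives no starting month for the 2020-2021 recruitment, and says data collection was extended because implementation was slow, so the schedule did respond to the delay. Recruitment could have begun late in 2020, with few women affected. No sentence says that an included woman attended a clinic not yet delivering the programme. This stands, and it is why the size can only be shown as a range. It does not remove the problem: extending collection adds later women, and nothing says that earlier ones were set aside.

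Several stronger readings are tempting and are not supported:

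- *That the estimate is diluted overall.* The article expects the pandemic to have raised mental ill-health in the same period, which could offset or exceed any dilution. It also already warns that fidelity varied between units.
- *That Objective 1 dropped 2020 because of roll-out.* Its stated reasons are representative data and countering COVID-19.
- *That the authors concede the point by writing "This shortfall contrasted with the implementation phase, during which we successfully recruited 942 participants".* This may be loose wording; elsewhere the article calls the same period postimplementation.
- *That the pilot contaminated the 2019 group.* The pilot is undated, and nothing places a 2019 participant in it.
- *That an established-against-pre contrast would reproduce Objective 1.* It would still differ in years, population (consenting Swedish speakers against all registered women) and outcome.

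It is also fair that the contrast in all 942 is a legitimate as-implemented estimate for a service evaluation, so there is no need to demote it. Clinic start dates are a detail that an article may leave to fuller documents. The windows and the single Objective 2 indicator, however, are fixed here.

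**Conclusion.** The point holds as a limited one. The article itself sets a 2020-2021 postimplementation group beside a spring 2020 start, early fidelity difficulties and slow implementation, and it uses a different later period for Objective 1. Some of the 942 may have been only partly exposed, which taken alone would move the Objective 2-4 contrasts toward no effect. The share is unknown, and so is the net direction once COVID-19 is considered.

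The illustration shows why it is worth handling: Objective 2 has power of about 81% at its own target ratio, and under the assumptions above an unexposed share of 25% would take that to about 61%, against 76% with those women set apart. These figures apply to the Objective 2 hazard ratio only. No size is claimed for Objectives 3 and 4, where the same group is used with other outcomes.

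**What to change.** Keep the all-942 contrast. For Objectives 2-4, prespecify in addition a period variable with three levels (pre, roll-out, established), set from each woman's first-visit date and her clinic's start date where that is available, and otherwise by 2020 against 2021. Report established against pre alongside the all-942 estimate. Add a sentence saying why the postimplementation window differs from that of Objective 1.

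First-visit date is an imperfect marker, because the mental health questions are repeated at gestational week 33 and a woman who booked early may have met the programme later. The 2020/2021 split is also only a proxy, since no date is given for the end of roll-out. Neither split removes the pandemic effect.

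The change needs dates and analysis wording, with no new recruitment, and the Objective 2-3 record review is still planned for 2025-2026. The price is fewer women in the established group and a somewhat wider interval for that contrast.
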